### 2.6. Clinical Assessments and Laboratory Investigations

#### 2.6.1. Blood Sampling and Analyses

Fasted blood samples will be collected via venepuncture into Vacuette^®^ blood tubes by an experienced phlebotomist. Samples will be centrifuged (Heraeus Biofuge Stratos, Germany, Heidelberg, sourced from Australia) for 15 min at 3000× *g* at 4 °C. Plasma, red blood cells, and buffy coat fractions will be aliquoted and stored at −80 °C until further analysis. Biochemical parameters, such as lipids (total cholesterol, LDL-cholesterol, HDL-cholesterol, triglycerides, and total-cholesterol-to-HDL-cholesterol ratio); glycaemic indices (glucose, insulin, and HbA1c); vitamin D (25-hydroxy vitamin D); full blood count; liver function, and high-sensitive C-reactive protein will be measured on a VP auto analyser using standardized reagents by the commercial pathology service provider NSW Health Pathology–North. Pro-inflammatory mediators, such as interleukin, tumour necrosis factor α, and intercellular adhesion molecule-1, will be quantified by enzyme-linked immunosorbent assay as per the manufacturer’s instructions (Abcam, Cambridge, UK) at the Nutraceuticals Research Program, University of Newcastle, (Callaghan, NSW, Australia). Polygenic risk scores will be measured to predict the likelihood of specific outcomes by including DNA variants in a statistical model.

#### 2.6.2. Anthropometry and Blood Pressure

Height will be measured using a wall-mounted stadiometer with a movable head piece (Seca 206 Bodymeter Wall Height Measure Ruler, Hamburg, Germany, sourced from Australia). Height (cm) and weight (kg) will be collected to the nearest 0.1 units in light clothing without shoes. A tensible tape measure positioned midway between the lower rib margin and the iliac crest (approximately in line with the bellybutton) horizontally will be used to measure waist circumference (cm). Blood pressure will be measured in the seated position, and three serial measurements with 1-min rests in between will be collected from a supported left arm of a rested participant. The first measurement will be discarded, and an average of the remaining two will be considered as the final measurement.

#### 2.6.3. Body Composition

Body mass and composition will be measured via dual-energy X-ray absorptiometry (DXA) using the GE Lunar Prodigy DXA machine (narrow angle fan beam technology) at the Newcastle Bone Density Centre, which is a private medical imaging centre in Newcastle. Body mass (kg), fat mass (kg), fat percentage, fat mass index, lean muscle mass (kg), lean muscle mass percentage, lean muscle mass index, body mass index (kg/m^2^), android/gynoid fat tissue distribution (% and ratio), waist-to-hip ratio, relative skeletal muscle index (kg/m^2^), bone mass (kg), and bone mineral density (g/cm^2^) will be quantified. At the Newcastle Bone Density Centre, all scans will be performed by qualified and experienced clinicians. Participants will attend the centre once, either on the same day or no more than 1–2 days of their clinic appointment at the University of Newcastle.

#### 2.6.4. Dietary Assessment

The Australian Eating Survey^®^ (AES) is a self-administered, validated, and reliable FFQ used to measure usual food and nutrient intake over the past 3 to 6 months [14]. The AES will be used to categorise dietary patterns, investigate the dietary profile of various dietary patterns, and assess diet quality and nutrient intake. The AES FFQ uses a subset of 70 questions related to core nutrient-dense foods recommended in the Australian Dietary Guidelines [23] and has been evaluated in Australian populations from the age of two years and is based on 15 years of research [14]. The Australian Recommended Food Score (ARFS) will be used to investigate diet quality across dietary patterns groups. The ARFS is derived from the AES FFQ by summing the points within eight sub-scales, as previously reported [24]. A comprehensive diet history capturing habitual food, beverage, and supplement intake for two typical days will also be collected during the appointment with the study coordinator who is also an Accredited Practising Dietitian and Accredited Nutritionist. An average of nutrient intake across the two days will be used to confirm findings from the FFQ, including directive questioning around motivations towards dietary patterns, such as *‘How long have you been consuming this type of dietary pattern?*’, ‘*What made you commence eating this type of dietary pattern?’,* and, when relevant, *‘What dietary pattern where you previously following?’* Other characteristics around dietary patterns will also be summarised, for example, frequency of consumption of dairy alternatives, plant-based meat alternatives, and their fortification status. Dietary pattern data from the AES and diet histories will be compared against the current 2013 Australian Dietary Guidelines (qualitatively) [23], and macronutrient and micronutrient data will be compared against the Nutrient Reference Values for Australia and New Zealand (quantitatively) [25]. Dietary intakes assessed from diet histories will be summarised and quantified using FoodWorks (Xyris^®^, Brisbane, Australia, sourced online).

#### 2.6.5. Medical History, Demographics, and Physical Activity

A self-administered medical history and demographic questionnaire will collect information regarding past and present medical conditions, including family history of CVDs; prescribed or over-the-counter medication(s); habitual supplement use; habitual consumption of alcohol; ethnicity; marital and occupation status; and level of education and income. Data required for the CVD risk prediction models will also be collected from the medical history and demographic questionnaire, such as diabetes status (defined as current treatment with oral anti-diabetic medications or insulin and confirmed by reported diagnosis from the participant’s general practitioner), smoking status, and report of antihypertensive medication prescribed for high blood pressure/hypertension. The International Physical Activity Questionnaire (IPAQ, Long Version October 2002) is a self-administered and validated questionnaire that asks participants to reflect on their physical activity levels in the last 7 days [13]. This will be used to assess habitual physical activity levels. Physical activity data will be interpreted as metabolic equivalent of task minutes per week (MET/week) to measure the energy cost of physical activities.

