## 2. Materials and Methods

### 2.1. Study Design and Setting

The PBDS is a cross-sectional study conducted at the Nutraceuticals Research Program, School of Biomedical Sciences & Pharmacy, University of Newcastle, Callaghan NSW, Australia. Eligible participants (Table 1) will be invited for one timepoint of data collection to examine the dietary profile, diet quality, nutritional status, and risk of developing CVD in adults consuming various PBDs and regular meat-eating diets (RMDs). To enhance representativeness of the Australian adult population and to gain a true understanding of the characteristics of the dietary patterns of interest, every effort will be made to invite all eligible individuals to participate in the study, including those with chronic health conditions.

**Table 1 nutrients-15-02850-t001:** Inclusion and exclusion criteria for the PBDS.

Inclusion Criteria	Exclusion Criteria
Adults ages 35–75 years.	Ages <35 and >75 years.
No history of CVD, such as myocardial infarction, coronary insufficiency, angina, ischaemic stroke, transient ischaemic attack, haemorrhagic stroke, peripheral artery disease, heart failure, or pacemaker implant.	Receiving treatment for CVDs.
Consuming one of the following dietary patterns in Table 2 for at least 6 months; (1) vegan, (2) lacto-ovo vegetarian, (3) semi-vegetarian, (4) pesco-vegetarian, and (5) regular meat-eaters.	Made significant changes to their dietary pattern, food choices, lifestyle and/or physical activity levels in the past 6 months (determined by an Accredited Practising Dietitian) and/or practicing in (or in the last 30 days) another research trial involving dietary and/or physical activity intervention.
	Pregnant/lactating.

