### 2.3. Study Regime

Data will be collected from consented enrolled participants once via two locations on the same day (or no more than 1–2 days apart) after an overnight fast (~10–12 h). First, body composition and bone density will be measured by a trained technician at the Newcastle Bone Density Centre (Waratah, NSW, Australia), and the remaining measurements and data will be collected at the Nutraceuticals Research Program at the University of Newcastle (Callaghan, NSW, Australia). These measurements will be conducted by the lead investigator and include seated blood pressure; waist circumference; diet history; medical, demographic, ethnicity, and physical activity history; and fasted blood samples for lipaemic parameters (total cholesterol, LDL-cholesterol, HDL-cholesterol, triglycerides, and total:HDL-cholesterol ratio), glycaemic parameters (glucose, insulin, and HbA1c), pro-inflammatory mediators (e.g., tumour necrosis factors alpha (TNF-α)), high-sensitivity C-reactive protein (hsCRP), full blood count, vitamin D, and liver function (Figure 1). Table 3 summarises data collected by participants unaided via self-administered questionnaires and data collected with assistance of a study investigator. All questionnaires have been either used in routine clinical care or were previously validated, and references are included within the tables, where appropriate. This cross-sectional study collects information from a singular time-point. Participants will be asked to provide consent to be contacted for potential future research.

The data will be stored on the University of Newcastle’s secure cloud-based system, which is suitable to host files that have large data or computing requirements. All electronic files will be password-protected as will be any study computers or laptops used for data entry in the first instance. The lead study investigator will enter the data, and double data entry and random cross-validation methods on the dataset will be routinely implemented to ensure validity, accuracy, and quality of the data.

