### 2.4. Primary Outcomes

The primary outcome of this study is the 10-year and 5-year risk of developing CVD.

The Framingham Risk Equation (2008) [15] is a single multivariable risk function that will be used to calculate the 10-year risk of developing atherosclerotic CVDs defined as coronary death, myocardial infarction, coronary insufficiency, angina, ischaemic stroke, transient ischaemic attack, haemorrhagic stroke, peripheral artery disease, and heart failure. This equation was developed from the long-running Framingham Heart Study and is targeted at individuals aged 30 to 74 years of age without CVD at baseline examination [16]. There are two versions of the equation; the version which uses lipids will be used for this study. Variables that are required for the equation include (1) sex; (2) age; (3) total cholesterol; (4) HDL-cholesterol; (5) systolic blood pressure; (6) treatment status for hypertension; (7) smoking status; and (8) diabetes status. The Framingham Risk Equation has been validated in non-Indigenous Australian adults, with the 2008 equation reported to perform better than previous Framingham Risk equations at predicting cardiovascular outcomes in relatively young, healthy Australians. Therefore, the 2008 Framingham Risk Equation will be used for this study [17].

The 5-year absolute CVD risk will be estimated using the Australian Absolute CVD Risk Calculator [18] developed by the National Stroke Foundation on behalf of the National Vascular Disease Prevention Alliance (NVDPA), now part of the Australian Chronic Disease Prevention Alliance (ACDPA), with partner agencies and expert clinicians [19]. The Australian Absolute CVD Risk Calculator is also based on the Framingham Risk Equation. Descriptors of risk categories in the Australian context will be defined as in the Guidelines for the Assessment of Absolute Cardiovascular Disease Risk (2009) [19,20] and are presented in Table 4.

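### The diabetes input to the primary risk scores requires drug treatment, so diagnosed-but-untreated and laboratory-evident diabetes is scored as no diabetes although the data to identify it are collected

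*Protocol article*

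**What the plan says.** Section 2.4 makes the 10-year and 5-year CVD risks the primary outcome. Its list of variables needed for the 10-year equation ends with "7) smoking status; and (8) diabetes status". Of the 5-year score it says "The Australian Absolute CVD Risk Calculator is also based on the Framingham Risk Equation".

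Section 2.6.5 gives the source of the diabetes input: "Data required for the CVD risk prediction models will also be collected from the medical history and demographic questionnaire, such as diabetes status". The same sentence defines that status as "defined as current treatment with oral anti-diabetic medications or insulin and confirmed by reported diagnosis", the diagnosis being one made by the participant's general practitioner. The questionnaire also records past and present medical conditions and medications.

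Section 2.3 includes "glycaemic parameters (glucose, insulin, and HbA1c" among the fasted blood measures, and section 2.6.1 names the same three tests for the pathology provider. No section uses these results to set or check diabetes status. Section 2.8 only compares blood parameters across diet groups.

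Table 1 does not exclude people with diabetes, and section 2.1 says that "every effort will be made to invite all eligible individuals to participate in the study, including those with chronic health conditions".

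**The concern.** Treatment and diagnosis are joined by 'and', so both are needed. Three kinds of participant are then coded as non-diabetic:

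- those with diagnosed diabetes managed without drugs, who fail the treatment condition;
- those with diagnosed diabetes treated only with a non-insulin injectable, who also fail it as worded;
- those with undiagnosed diabetes, who fail both conditions whatever their study glucose or HbA1c shows.

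This is a stated rule, not a detail left to a later document, and it feeds the primary outcome. The study could report a diabetic-range HbA1c among its secondary outcomes and score the same person as non-diabetic in the primary one.

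The error need not be even across groups. The rule separates drug-managed from otherwise managed diabetes in a study whose exposure is diet. The Introduction also reports, from the authors' earlier cohort of women, that diabetes was less prevalent in vegetarians and that impaired glucose tolerance was more prevalent in high-quantity meat consumers. An uneven error would bias the group contrast as well as add noise.

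**Working it through.** **The plan's own figure.** Section 2.7 gives a mean 10-year score of 13.3, SD 5.77, target difference 3.33 (25% × 13.3 = 3.325), 80% power and a 0.05 significance level. Taking the test as two-sided:

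n per group = 2 × [5.77 × (1.960 + 0.842) / 3.33]² = 47.1, rounded up to 48; 48 × 5 = 240.

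This reproduces the plan. Power at 48 per group is 0.807 by the normal approximation and 0.799 by the t-test. The diabetes rule does not affect the planned number.

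**Who is missed under each reading.**

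| Participant | Rule as written (treatment and diagnosis) | Looser reading (diagnosis alone enough) |
|---|---|---|
| Diagnosed, on oral drug or insulin | diabetic | diabetic |
| Diagnosed, no such drug | non-diabetic | diabetic |
| Undiagnosed, study result in diabetic range | non-diabetic | non-diabetic |

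Even the looser reading leaves the last row wrong.

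**Effect on one participant.** Assume that diabetes multiplies the score by m = 1.5 to 2 (not in the documents). A recorded 13.3 should then be 13.3 × 1.5 = 19.95 to 13.3 × 2 = 26.6, so the score is 33 to 50% too low. Whether this changes the Table 4 category depends on m. A recorded 12% that should be 18% stays intermediate; one that should be 24% belongs in the high category.

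**Effect on a two-group comparison.** Let u be the difference between two groups in the share of participants with missed diabetes (also an assumption). Then:

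shift = 13.3 × (m − 1) × u

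| u | Shift, m = 1.5 | Shift, m = 2 | Share of 3.33 |
|---|---|---|---|
| 1% | 0.07 | 0.13 | 2 to 4% |
| 3% | 0.20 | 0.40 | 6 to 12% |
| 4% | 0.27 | 0.53 | 8 to 16% |
| 5% | 0.33 | 0.67 | 10 to 20% |
| 10% | 0.67 | 1.33 | 20 to 40% |

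Here 13.3 stands for the recorded score of a missed case, since that is what the rule produces. Treating it as the true score would understate the shift: at u = 4%, 13.3 × 0.04 × (1/3 to 1/2) = 0.18 to 0.27.

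**Against sampling error.** SE of a difference between two groups of 48 = 5.77 × √(2/48) = 1.18. The shift at u = 4% is therefore 0.27/1.18 = 0.23 to 0.53/1.18 = 0.45 standard errors. In people, 4% of 48 is about two participants.

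**Power, if the shift shrinks a true difference of 3.33.** Power falls from 0.81 to 0.79 at u = 1%, m = 1.5; to between 0.76 and 0.70 at u = 3%; and to 0.40 at u = 10%, m = 2. If the shift runs the other way, the same number of points is added to the contrast.

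**The case against.** The strongest objection concerns the remedy. A published risk equation should receive the diabetes definition it was built with. Those definitions are in the cited sources, not in the article, so a broader definition cannot be assumed correct for either score. This stands, and the fix is made conditional on it. It does not rescue the present rule, because the article nowhere says that either score's specification requires drug treatment.

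Second, a reader might infer that the rule favours the study hypothesis, because people who control diabetes through a plant-based diet are the ones coded as non-diabetic. The documents do not support that. They give no data on how diabetes is managed in each diet group. The findings cited in the Introduction could equally mean that undiagnosed cases are commoner among meat-eaters. Missing those would lower the meat-eaters' scores and shrink the contrast. The two mechanisms pull in opposite directions.

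Third, few participants may be affected, and both the multiplier and the missed shares are assumptions. This stands and limits the severity.

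Fourth, the study has partial safeguards: diagnoses are recorded, and glycaemic measures are compared across groups, so an imbalance could be seen. That makes the error detectable, but nothing in the plan carries it back into the scores.

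**Conclusion.** The rule is fixed too narrowly and should be changed before the scores are computed. Followed as written, it codes diagnosed diabetes managed without the named drugs, and diabetes evident only from the study blood tests, as absent in the primary outcome.

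The misclassification may differ between diet groups, but its direction cannot be derived from the documents. Missed diet-managed cases in the plant-based groups would exaggerate the contrast; missed undiagnosed cases among meat-eaters would reduce it.

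The group-level effect is probably modest. The upper end of the range tabulated above needs both a doubling of the score and a 10-point imbalance in missed cases. Every figure in that range rests on the assumed multiplier and imbalance. The sample size calculation is unaffected.

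**What to change.** For the primary scores, code diabetes as present if any of these holds: a reported doctor diagnosis; any glucose-lowering medication; or a study fasting glucose or HbA1c at or above the laboratory's diagnostic threshold. First check this against each score's own specification of its diabetes input, and state the result of that check for the 10-year and the 5-year score separately. Report the treatment-only coding as a sensitivity analysis. If a score's specification is narrower, use that specification for the primary score and make the broader coding the sensitivity analysis. In either case, give the number of participants reclassified in each diet group, which shows the imbalance directly.

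The cost is one definition and one repeat of the score calculation, with no new data. Section 3 places data cleaning, coding and analysis after recruitment and data collection, so the change fits the timetable. The downside is that a single laboratory value may over-classify a few participants; reporting both codings shows how much this matters.

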### 2.7. Sample Size

Based on previous estimates of variance in 10-year CVD risk scores using the Framingham algorithm (Mean = 13.3, SD ± 5.77) [26] to elicit 80% power at a significance level of 0.05 to detect a 25% (Δ = 3.33) difference in CVD risk scores among at least one group following a PBD pattern compared with a regular meat-eating dietary pattern, a sample size of *n* = 240 participants (48 per dietary pattern) is required. Previous observational studies on dietary pattern and lifestyle have reported differences of 27% and 20–22% in Framingham Risk Scores [27,28]. Moreover, we have reported reductions of 13–23% in RCTs following dietary interventions for only 3–4 weeks [29,30]. A longitudinal study which employed a healthy PBD index reported a 47–68% lower risk of developing CVD in individuals among the 2nd and 3rd tertiles of adherence to a healthful PBD compared with their 1st tertile counterparts [31]. Similarly, vegetarians have been shown to have a 22% lower rate of ischaemic heart disease than meat-eaters in the EPIC-Oxford study of more than 48,000 participants followed up after 18 years [32]. Therefore, after review of previous studies’ CVD risk outcomes, the authors arrived at the 25% estimated difference in Framingham Risk Score between at least the two extreme dietary patterns (vegan vs. regular meat-eating diet). This cross-sectional study meets the target sample size of 48 per group to be statistically powered, and estimates are substantially supported by the previous literature. Authors recognise that the modest sample size of 240 may be used as a pilot or ‘proof of concept’ study for larger cohorts in the future.

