### 2.8. Statistical Analyses

All data will be assessed for normality by inspecting visual plots, such as histograms, quantile plots, and Q-Q plots, within each dietary pattern group for each variable. One-way ANOVA or Kruskal–Wallis tests will be used for comparison of CVD risk scores, dietary intake, and cardiometabolic parameters, including all clinical measures, medical/demographics, and blood parameters across dietary pattern groups. Chi-square or Fisher’s Exact tests will be used to compare qualitative dietary intake data and other categorical data across dietary pattern groups. Directed acyclic graphs (DAGs) will be used to display dependencies between outcome (5-year absolute CVD risk and 10-year CVD risk scores), exposure (different categories of dietary patterns determined via classifications presented in Table 1), and confounding/mediating variables to determine the minimum set of variables necessary to control for confounding [33] (Figure 2). Linear regression will be used to account for potential confounding factors described in the DAGs, such as age, sex, alcohol use, smoking status, and physical activity levels. Mediation analysis will be used to estimate the effect of PBDs on CVD risk that is not mediated through BMI [33,34]. Predictably, there will be intrinsic differences between dietary pattern groups, as the study design endeavours to evaluate the true characteristic of each group (chronic diseases, lifestyle choices, etc.). To address this and remove risk of overadjustment, a sensitivity analysis will be performed on potential additional important confounding variables not already identified in the DAGs to assess how robust the results are when comparting the additional confounding factor [35,36]. *p*-values will be adjusted using the Benjamini–Hochberg method to control the False Discovery Rate to 5%.

All statistical analyses will be conducted using StataCorp. 2015. *Stata Statistical Software: Release 14* (College Station, TX, USA: StataCorp LP). Continuous data will be presented as means, SD, median, and interquartile range (25th–75th percentile), and categorical data will be summarised as frequencies and percentages.

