The PBDS commenced recruitment on 10 November 2021, and despite having some delay due to the COVID-19 pandemic, we have been able to recruit individuals from the community, with several participants already enrolled into each of the dietary pattern categories. The study remains in the recruitment and data collection phase until at least mid-2023 before data cleaning, coding, and analyses will commence. The study is expected to be completed by mid-2024. As with many observational studies, some of the data collected in this study are self-reported; however, several of the data collection tools employed in this study have been validated in Australian populations. To further mitigate any risk associated with self-reported data, all data are cross-checked by study researchers and clarified (when required) with participants to their ensure accuracy and the correct interpretation of the questionnaires or instructions. As with all cross-sectional population-based studies, caution must be exercised when inferring causation from the results. As detailed in the protocol, appropriate statistical analyses will be conducted to summarise and adjust for the confounding factors and covariates, and a senior biostatistician will be involved in the project.

To conclude, given several strengths and the significance of this study’s findings, albeit with some limitations, analysis of the data arising from this study will likely influence nutrition policy and dietetic practice around the influence of ‘plant-forward’ eating patterns for heart health.

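### The 80% power for 48 per group belongs to one unadjusted two-group comparison of the 10-year score, not to the five-group and FDR-adjusted tests that the plan describes

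*Protocol article*

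**What the plan says.** Section 2.7 (Sample Size) bases the number on the 10-year Framingham score, with mean 13.3 and SD 5.77. Power is set at 80% with α 0.05, and the aim is "to detect a 25% (Δ = 3.33) difference in CVD risk scores among at least one group following a PBD pattern" against regular meat-eaters. The section arrives at 240, or 48 in each of five groups. The 25% is then tied to a "difference in Framingham Risk Score between at least the two extreme dietary patterns (vegan vs. regular meat-eating diet"). No means are given for the other three groups.

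The tests are described elsewhere:
- Section 2.4: "The primary outcome of this study is the 10-year and 5-year risk of developing CVD", which makes two scores.
- Section 2.8: risk scores are compared across the dietary groups by one-way ANOVA or Kruskal–Wallis. Confounder-adjusted linear regression follows.
- Section 2.8 also says that p-values "will be adjusted using the Benjamini–Hochberg method to control the False Discovery Rate to 5"%. It does not say which tests form the family.

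Section 2.7 also states: "This cross-sectional study meets the target sample size of 48 per group to be statistically powered". The Discussion (section 3) reports: "The study remains in the recruitment and data collection phase until at least mid-2023".

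**The concern.** A power figure belongs to a particular test of a particular hypothesis. Section 2.7 mentions neither the five-group test, nor the BH adjustment, nor the 5-year score, yet it presents 80% as the power of the study. If the planned tests have less, a non-significant result could be read as evidence of no difference from an adequately powered study. That matters here because the article expects its findings to inform dietary guidelines and policy.

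The sentence saying the target is met adds to this. It reads as if the numbers had been secured, while the Discussion describes a study still recruiting.

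**Working it through.** **Inputs.** From section 2.7: SD 5.77, mean 13.3, Δ = 3.33 (25% × 13.3 = 3.325, rounded up), 48 per group, α 0.05, power 80%. Assumed: two-sided α (one-sided would give 38 per group, so two-sided fits), common SD, approximately normal scores, no missing data.

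**1. Reproducing the plan's figure.**
- d = 3.33 / 5.77 = 0.577.
- n = 2(1.960 + 0.842)² / 0.577² = 47.1, so 48 per group; 5 × 48 = 240.
- Exact two-sample t power at 48 per group (df 94, noncentrality 3.33 / (5.77√(2/48)) = 2.83) is 79.9%.

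The stated number is therefore the two-group formula multiplied up to five groups.

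**2. Five-group ANOVA at 0.05.** Noncentrality λ = 48 × Σ(mᵢ − m̄)² / 5.77², with df 4 and 235. The largest gap between groups is 3.33 throughout, and Δ² = 11.089.

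| Pattern of means | Σ(mᵢ − m̄)² | λ | Power | Per group for 80% |
|---|---|---|---|---|
| Two extremes, three midway | 0.5Δ² = 5.54 | 7.99 | 59% | 73 (365 total) |
| Evenly graded | 0.625Δ² = 6.93 | 9.99 | 71% | 59 (295 total) |
| One group apart from four equal | 0.8Δ² = 8.87 | 12.79 | 82% | 46 (230 total) |
| Two versus three | 1.2Δ² = 13.31 | 19.18 | 95% | 31 (155 total) |

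**3. BH over the two primary scores.** This was simulated with the same standardised effect on both scores (the article gives no SD for the 5-year score) and correlations of 0.5 to 0.95. ANOVA power for one score is about 54–56% (midway), 67–68% (graded) and 79–80% (one group apart).

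**4. BH over the four comparisons with meat-eaters, one score.** This was simulated with pooled variance on 235 df. The family is assumed, because the article does not state it.

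| Pattern | Vegan vs meat-eater | At least one plant-based group |
|---|---|---|
| Only vegan differs | 62–63% | 64% |
| Others midway | 65% | 67% |
| Evenly graded | 66% | 70% |
| Two plant-based groups differ | 69% | 80% |
| All four plant-based groups differ | 76% | 90% |

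The contrast used to justify Δ stays below 80% in every pattern tried. The looser target of at least one plant-based group reaches 80% only when two or more of those groups differ from meat-eaters by the full 3.33.

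**5. Recruitment wording.** Section 2.7 says the target is met. The abstract says 240 adults will be recruited, and section 3 says recruitment continues. These cannot all be literally true at the time of writing.

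**The case against.** The strongest reply is that the ANOVA result depends on three means the article never gives. If one group stands apart, the omnibus test has 82% power, and 79–80% after BH over two correlated scores, so the stated 80% survives. A two-versus-three split gives 95%. This stands, and it rules out any single figure for the power of the plan. But section 2.7 itself calls vegan and regular meat-eating the extremes. That most naturally places the others between them, where power is 59–71%, though it does not exclude groups level with an extreme.

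Second, the planned regression adjusts for age, sex and smoking, which are inputs to the Framingham score and should reduce residual variance. If they explained 20%, 30% or 40% of it, λ would be divided by 0.8, 0.7 or 0.6. Midway power would rise to 71%, 77% or 84%, and graded power to 81%, 87% or 92%, before any loss from covariate imbalance between groups. This is a fair possibility, but the R² values are assumptions and section 2.7 makes no such claim.

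Third, the BH family may be set in an analysis plan that is not shown, so its absence here is not an error. That does not rescue a power figure that ignores BH altogether.

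Fourth, section 2.7 concedes that the sample is modest and may serve as a pilot. The 80% claim still stands beside that remark.

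A reader might also pool all secondary tests with the primary ones and infer power near 30%. That needs an invented family (for example 60 tests) with no other true effect. The article defines no such family. Zero other effects is also implausible, because the groups are defined by what they eat and dietary intake is among the variables compared.

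**Conclusion.** The point holds as a mismatch between the sample-size statement and the planned tests. The 80% is the power of one unadjusted two-sided comparison of two groups on the 10-year score (79.9%). Unadjusted ANOVA power is about 59–71% with vegan and meat-eater as extremes and the others between them, and 82% or 95% under the other two patterns. With BH over four comparisons with meat-eaters, power is about 62–76% for the vegan contrast and 64–90% for at least one plant-based group.

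The documents do not support the stronger inference that the study falls short of 80% whatever the true means. The figures rest on SD 5.77, Δ = 3.33, 48 complete participants per group, no covariate adjustment and, for the contrasts, an assumed BH family. Kruskal–Wallis power was not computed. The recruitment sentence is a smaller, separate inconsistency, and the abstract and Discussion make the true status clear.

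**What to change.** In section 2.7, state that 80% applies to a single unadjusted, two-sided vegan versus regular meat-eater comparison of the 10-year score. Then give the power of the planned ANOVA and of the BH-adjusted contrasts, with the five assumed means and the BH family behind each figure, and say how the 5-year score is treated. If covariate adjustment is to be relied on for power, state the assumed R².

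Alternatively, the sponsor may name that one contrast on the 10-year score as the primary test, outside the BH family. This matches the existing calculation, but the 5-year score and the other contrasts become secondary. It is a design choice, not the only valid remedy.

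In either case, reword the sentence on meeting the target to say that the study aims to recruit 48 per group. The cost is rewording of section 2.7, plus 2.4 and 2.8 under the alternative. No extra participants are needed, but under the first option the study may have to report power below 80% for its planned tests.
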